## Abstract

**Introduction:** The prevention of schizophrenia and other psychotic disorders has led researchers to focus on early identification of individuals at clinical high risk (CHR) for psychosis and to treat the at-risk symptoms in the pre-psychotic period. Although at-risk symptoms such as attenuated hallucinations or delusions are common in adolescents and associated with a marked reduction in global functioning, the evidence base of effective interventions for adolescents at CHR state and even ﬁrst-episode psychosis is limited. Thus, the present protocol describes a study design that combines therapy modules for CHR adolescents with a smartphone application supporting the young individuals between the therapy sessions. The treatment approach “Robin” is based on existing therapy strategies for adolescents with first episode of psychosis and the available recommendations for adults with at-risk symptoms.

**Methods:** The evaluation aims firstly to compare the efficacy of Robin in 30 CHR adolescents aged 14–18 to an active control group (treatment as usual) from a previous study. Primary outcome measures will be at-risk symptomatology, comorbid diagnosis, functioning, self-efficacy, and quality of life. For the prospective intervention condition (16 weekly individual sessions + a minimum 4 family sessions), help-seeking adolescents with CHR for psychosis, aged 14–18, will be recruited over 3 years. At-risk and comorbid symptoms, functioning, self-efficacy, and quality of life are monitored at six time points (baseline, during the treatment period; immediately after intervention; and 6, 12, and 24 months later) and compared with the respective measures of the active control group.

**Discussion:** To the best of our knowledge, this is the first controlled trial to test the efficacy of a specific early psychosis treatment in combination with a smartphone application for adolescents at CHR for developing psychosis. The results of the study are expected to add information that may substantially decrease the burden of CHR adolescents and increase their resilience. It may offer age-adapted and targeted strategies to guide clinicians in the treatment of these vulnerable individuals. Furthermore, research in the field of early intervention will be enriched by our findings.

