## Introduction

Psychotic disorders are severe mental illnesses that typically emerge in late adolescence or early adulthood (1). The disorders lead to considerable social and economic deficits, as well as burden for the individual and family (2). Prior to the onset of the first psychotic episode, the majority of the individuals experience attenuated psychotic symptoms, known as at-risk symptoms (3).

Two different sets of clinical high risk (CHR) criteria have been developed for the purpose of early identification of individuals at CHR: 1) the basic symptom criteria focusing on subtle, subjectively experienced changes in cognition and perception and 2) the ultra-high-risk criteria, such as attenuated positive symptoms indicating the imminent manifestation of psychosis (4). In the present article, we use the term CHR state, which includes both of these current risk concepts.

There is an ongoing discussion as to whether or not to treat at-risk symptoms (5–7). The rates of CHR individuals transitioning to psychotic disorders have declined over the years of early detection research (8), and the specificity of at-risk symptoms is questioned (5, 9). At-risk symptoms are common in the general population, particularly during adolescence; it is a clinical challenge as to how to differentiate between young people who are at risk and those who are not (10, 11). Nevertheless, leading experts in the field of early intervention in psychosis have claimed that treatment of at-risk symptoms in the help-seeking population is justified independently of the risk of conversion to psychosis [for example, Refs. (12–15)].

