In the treatment of psychotic disorders, the first research results from the use of smartphone applications are promising (62, 64–68); however, there is little known about mobile technologies addressing at-risk symptoms (50). Despite current analysis demonstrating young people would be interested in using mobile technologies, there is a lack of investigations with this population (49, 51). The available studies have shown a high acceptance and subjective satisfaction with mobile interventions in young people with psychiatric problems (57, 61, 69).

There is great heterogeneity across symptomology and functioning in the CHR population (30, 70). As a consequence, individualized adaptive treatment approaches are required. While some individuals will respond to an intervention, others will not. Robin is an individually tailored approach, and the treatment is personalized to the individuals’ special needs depending on their stage of illness, presence of comorbidities, or functional impairment.

The current clinical trial “Evaluation of the Treatment program Robin” (ETRo) has two main study goals:

to investigate the feasibility and impact of the combined treatment program: the structured therapy and the smartphone application; andto investigate the efficacy of this specific intervention versus treatment as usual (TAU).

Hypotheses of the study:

Hypothesis 1: Robin is feasible and accepted in this young population of CHR individuals. The adolescents will show high treatment engagement.Hypothesis 2: Robin improves the quality of life and self-efficacy at 6-, 12-, and 24‐month follow-up in individuals with CHR compared with individuals with CHR who received TAU.Hypothesis 3: Robin enhances the rate of adolescents with clinical and psychosocial functional remission at 6-, 12-, and 24‐month follow-up than does TAU.

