### Primary Outcome

Primary outcome measures are transition to psychotic disorders, changes in at-risk as well as comorbid symptomatology, global functioning, life quality, and self-efficacy. All these measures will be compared with those of the control group.

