### Clinical Analyses

Differences in the primary and secondary outcomes between the two study groups at all time points will be examined with repeated measures analysis of variance and standardized effect sizes (Cohen’s *d*) will be reported. Their respective confidence intervals will be calculated for comparison. Response and remission rates will be compared across groups with contingency tables and differences tested with χ^2^. All unidirectional hypotheses will be tested one sided; bidirectional hypotheses will be tested two sided. Alpha is set to *p* < 0.05. All analyses will be conducted within SPSS.

A linear mixed model approach will be used to assess differences in the primary and secondary outcomes between the two study groups. Logistic regression will be used to assess response and remission rates across the groups. Medication, education, and intelligence will be taken into account as confounding factors by including them in mixed model and logistic regression model, respectively. All unidirectional hypotheses will be tested one sided; bidirectional hypotheses will be tested two sided. Significance level α is set to 0.05.

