The integrated and age-adapted treatment approach as well as the focus on outcomes other than the putative progression of symptomatology and onset of psychosis also seems to be supported by a recent network meta-analysis. Davies et al. (89) compared efficacy of different preventive interventions in CHR individuals considering conversion rates in psychosis and acceptability of treatment intervention. The findings demonstrated a lack of evidence to favor a specific intervention to prevent onset of psychosis, and there were no significant differences in acceptability between the treatment approaches. In the context of non-superiority of any intervention, the authors questioned CBT as the most widely adopted intervention in the early intervention of psychosis.

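### Transition to psychosis is listed as a primary outcome, but the stated analysis does not fit it, the sample size does not cover it, and the 2010–2012 controls could make Robin look preventive

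*Protocol article*

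**What the plan says.** **Outcome status.** Primary Outcome puts transition first ("Primary outcome measures are transition to psychotic disorders"); the full list reads "Primary outcome measures are transition to psychotic disorders, changes in at-risk as well as comorbid symptomatology, global functioning, life quality, and self-efficacy", and the section adds that all of these are compared with the control group. The abstract reads "Primary outcome measures will be at-risk symptomatology, comorbid diagnosis, functioning, self-efficacy, and quality of life", without transition. None of the three hypotheses in the Introduction names transition; the nearest is Hypothesis 3, "Robin enhances the rate of adolescents with clinical and psychosocial functional remission". Standard Care lists the outcomes that the control study (ZInEP) measured comparably, and transition is not among them. The Discussion says the group chose to concentrate on quality of life, self-efficacy and functioning, and describes a "focus on outcomes other than the putative progression of symptomatology and onset of psychosis".

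**Analysis.** Clinical Analyses states "Differences in the primary and secondary outcomes between the two study groups at all time points will be examined with repeated measures analysis of variance", with Cohen's d, and then "A linear mixed model approach will be used to assess differences in the primary and secondary outcomes between the two study groups". Chi-square tests and logistic regression are named for response and remission rates only. Directional hypotheses are tested one-sided at 0.05.

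**Sample size.** Thirty per group, from assumed scale-score differences at 6 months (Table 2).

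**Calendar time.** The Introduction says "The rates of CHR individuals transitioning to psychotic disorders have declined over the years of early detection research". Controls were accrued from April 2010 to July 2012; Robin recruitment runs from September 2017 to September 2020.

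**The concern.** Transition happens at most once per patient. Everyone starts without it, because a psychotic disorder is an exclusion criterion. A mean-score model with Cohen's d does not describe such an outcome, yet those are the methods stated for primary outcomes.

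Two things are at stake. First, a non-significant difference in a primary outcome could be read as absence of effect when the trial was never sized to see one. Second, a lower rate under Robin could be read as prevention when part or all of it might come from calendar time. Matching on age and sex does not touch a calendar effect.

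**Working it through.** **1. The plan's own figure.** Table 2 gives 17 per group for SIPS (difference 15), 16 for SPI-CY (9) and 27 for SWE (4), raised to 30. The article prints neither SDs nor power, so these can only be solved backwards. With a two-sample t-test at alpha 0.05, from one-sided 80% power to two-sided 90% power, the implied SDs are 17.2 to 13.1 (SIPS), 10.0 to 7.6 (SPI-CY) and 5.8 to 4.5 (SWE). That neither confirms nor refutes the stated numbers, and none of them bears on a binary outcome. Transition is not an instrument in Table 2.

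**2. Power for transition.** Inputs from the article: 30 per group, alpha 0.05, one-sided for directional hypotheses. Input assumed: control risk 10–30%, halved by Robin.

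Normal approximation, with p̄ the mean of p1 and p2:

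power = Φ{ [(p1 − p2) − z·√(2p̄(1−p̄)/n)] / √[(p1(1−p1) + p2(1−p2))/n] }

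For 20% v 10%, two-sided: the null SE is √(2 × 0.15 × 0.85/30) = 0.0922 and the alternative SE is √((0.16 + 0.09)/30) = 0.0913. Then (0.10 − 1.96 × 0.0922)/0.0913 = −0.88, so power is 19%.

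Exact enumeration of all 31 × 31 outcomes (chi-square without continuity correction):

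| Control v Robin | Expected events | Chi-square, two-sided | Chi-square, one-sided | Fisher, two-sided |
|---|---|---|---|---|
| 10% v 5% | 3.0 + 1.5 | 11% | 19% | 2% |
| 20% v 10% | 6.0 + 3.0 | 19% | 31% | 10% |
| 30% v 15% | 9.0 + 4.5 | 28% | 42% | 19% |
| 20% v 5% | 6.0 + 1.5 | 45% | 59% | 24% |
| 30% v 5% | 9.0 + 1.5 | 78% | 87% | 63% |
| 20% v 0% | 6.0 + 0 | 88% | 96% | 57% |

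The first three rows are the halved risks; the last three are much larger effects. The chi-square columns are closest to the plan, since chi-square is the contingency-table test it names.

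**3. Size needed.** For 80% power, n per group = [z·√(2p̄(1−p̄)) + 0.842·√(p1(1−p1) + p2(1−p2))]² / (p1 − p2)². For 20% v 10%, two-sided: (1.96 × 0.505 + 0.842 × 0.5)²/0.01 ≈ 199 (157 one-sided). The same formula gives 435 (343) for 10% v 5% and 121 (95) for 30% v 15%. Conversely, by the normal approximation, detecting a halved risk with 80% power at 30 per group needs a control risk of about 71% two-sided or 63% one-sided.

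**4. Precision.** With 6 of 30 against 3 of 30, the simple 95% interval for the difference is 0.10 ± 1.96 × 0.0913, or −8 to +28 percentage points.

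**5. Calendar drift, illustration only.** Suppose Robin has no effect, but the underlying risk has fallen since the controls were accrued. The one-sided chi-square rejects in Robin's favour in 5.4% of trials at 20% v 20%, in 13.7% if the risk drifted to 15%, and in 30.6% if it drifted to 10%. These drifts are assumed; the article gives none.

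**The case against.** The ANOVA and mixed-model sentences are blanket wording in a condensed article. Read literally, they would also send hospitalization and therapy discontinuation to ANOVA. The binary methods are already in the plan, and the mapping of outcomes to models may be left to a fuller document. This stands in part: it is probably loose drafting. But the article does state a rule for primary outcomes, and that rule does not fit the first one it names.

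A reader might infer three stronger points that the documents do not support:

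- **That the trial has almost no power for transition.** This follows only from two-sided Fisher and modest effects. The chi-square test gives more, and for 20% v 0% it reaches 88–96%. All the rates are assumptions.
- **That the historical control does bias the comparison, so a lower Robin rate is to be expected.** The Introduction gives no years, size or centre for the decline and does not show that it continued from 2010–2012 to 2017–2020. Only 'could bias' is supported. The Discussion already admits possible bias from the non-randomized historical control and argues that the service and health system were unchanged; it does not mention the decline in transition.
- **That a null result would be uninformative.** A confidence interval still informs, though it would be wide.

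Finally, since the hypotheses and Discussion look elsewhere, a preventive claim may never be intended. That supports moving transition out of the primary list rather than keeping it there.

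**Conclusion.** The point holds in limited form. The article contradicts itself on whether transition is a primary outcome. The analysis it states for primary outcomes does not suit a one-time binary event, and the sample size was not derived for it. For a halved risk from an assumed 10–30%, power is about 11–28% two-sided or 19–42% one-sided by chi-square, and 2–19% by two-sided Fisher. Only very large effects are within reach. The calendar gap could favour Robin, in the direction the article's own Introduction suggests, but by an amount that cannot be determined from it. The scale-score outcomes on which the trial was sized are not affected by this point.

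**What to change.** 1. Make transition a secondary, descriptive outcome, and bring Primary Outcome, the abstract, the hypotheses and the Standard Care outcome list into agreement.
2. Exclude it explicitly from the repeated-measures ANOVA and the linear mixed model.
3. Report the cumulative proportion with transition by group at the visits both cohorts share (months 6, 12 and 24), with an exact 95% interval for each group and a confidence interval for the difference. Do not use event times from the month 2 and 4 visits. Only the Robin cohort has these, and they would date its events earlier than those of the controls.
4. Add to the Discussion's limitations that a lower rate than in the 2010–2012 controls could reflect a secular decline and is not by itself evidence of prevention.

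Cost: one fewer primary outcome, and, because the trial is registered and already recruiting, a documented amendment and registry update. Data collection does not change.

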### Secondary Outcome

Secondary outcome measures are the feasibility, user-friendliness, and acceptance of the treatment program Robin and the smartphone application Robin Z. Therefore, discontinuation of the therapy and subjective satisfaction with the therapy will be assessed. Furthermore, data about hospitalization, suicidality, and medication adherence will be collected and analyzed in comparison with those of the control group.

### Assessment

At baseline, demographic variables, past psychiatric illness, and treatment information are obtained from the participants and their caregivers. Before participating in the study, all patients will undergo a clinical assessment and diagnostic process according to *International Classification of Diseases*, Tenth Revision, criteria. Adolescents will be asked to complete a questionnaire about their personality traits PSSI (74) and to perform the Wechsler Intelligence Scale for Children (75) or Wechsler Adult Intelligence Scale for individuals aged > 16 years 11 months (76) to evaluate their cognitive profile.

In accordance with EPA guidance on the early detection of CHR states of psychoses, the CHR status is assessed with the Schizophrenia Proneness Interview Child and Youth Version (71) and the Structured Interview for Prodromal Syndromes (72). All investigators are either psychologists or psychiatrists. They are trained to a “gold standard,” and reliability will be measured for the duration of the trial. Comorbid mental disorders will be screened for with the Mini-International Neuropsychiatric Interview for Children and Adolescents based on *Diagnostic and Statistical Manual of Mental Disorders*, Fourth Edition (77). The severity of depression will be measured using theHamilton Depression Scale (78).

Information about functioning will be measured with the Global Assessment of Functioning Scale (GAF) (79), Social and Occupational Functioning Assessment (SOFA) Scale (80), and Global Functioning: Social Scale (GF: Social) (81). Data about quality of life, personality traits, and self-efficacy will be collected using the Manchester Short Assessment of Quality of Life (MANSA) (82) and the General Self-Efficacy Scale (SWE) (83).

Treatment satisfaction will be evaluated with the treatment evaluation questionnaire for adolescent patients FFB-J (84). A feedback form created specifically for the app will gather information regarding acceptance and contentment with the smartphone application Robin Z (**Table 1**).

**Table 1 T1:** Description of assessments from baseline to endpoint of study.

	Baseline	Intervention (16 session)		Follow-up		
**Time point (months)**	**0**	**2**	**4**	**6**	**12**	**24**
Socio‐demographic characteristics	x	x	x	X	x	x
Clinical diagnosis according to**** *ICD-10* Re-evaluation of all diagnoses	x	x	x	X	x	x
Medication	x	x	x	X	x	x
Intellectual ability: WISC/WAIS	x					
Personality traits: PSSI	x					x
Clinical High Risk State: SPI-CY SIPS	x x	x	x x	x x	x x	x x
Comorbidities: MINI KID	x	x	x	x	x	x
Depression: HAMD	x	x	x	x	x	x
Functioning: GAF, GF: Social SOFAS	x x x	x x x	x x x	x x x	x x x	x x x
Quality of Life: MANSA	x	x	x	x	x	x
Self-efficacy: SWE	x	x	x	x	x	x
Satisfaction with treatment: FFE Feedback form regarding app Robin			x x			

GAF, Global Assessment of Functioning Scale; GF, Social, Global Functioning: Social Scale; HAMD, Hamilton Depression Rating Scale; ICD-10, International Classification of Diseases, Tenth Revision; MANSA, Manchester Short Assessment of Quality of Life; SIPS, Structured Interview for Prodromal Syndromes; SOFAS, Social and Occupational Functioning Assessment Scale; SWE, General Self-Efficacy Scale; WAIS, Wechsler Adult Intelligence Scale; WISC, Wechsler Intelligence Scale for Children.

### Statistical Analysis

Statistical analysis will be reported in accordance with the Consolidated Standards of Reporting Trials statement.

### Clinical Analyses

Differences in the primary and secondary outcomes between the two study groups at all time points will be examined with repeated measures analysis of variance and standardized effect sizes (Cohen’s *d*) will be reported. Their respective confidence intervals will be calculated for comparison. Response and remission rates will be compared across groups with contingency tables and differences tested with χ^2^. All unidirectional hypotheses will be tested one sided; bidirectional hypotheses will be tested two sided. Alpha is set to *p* < 0.05. All analyses will be conducted within SPSS.

A linear mixed model approach will be used to assess differences in the primary and secondary outcomes between the two study groups. Logistic regression will be used to assess response and remission rates across the groups. Medication, education, and intelligence will be taken into account as confounding factors by including them in mixed model and logistic regression model, respectively. All unidirectional hypotheses will be tested one sided; bidirectional hypotheses will be tested two sided. Significance level α is set to 0.05.

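### Two inferential analyses are planned for the same outcomes at the same alpha and neither is named as deciding; the first leaves out the confounders that the plan names and does not fit the visit schedules

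*Protocol article*

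**What the plan says.** The Clinical Analyses section of the protocol article has two paragraphs.

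- **First paragraph.** The scope is "Differences in the primary and secondary outcomes between the two study groups at all time points", and these "will be examined with repeated measures analysis of variance and standardized effect sizes" (Cohen's d, with confidence intervals). For binary outcomes: "Response and remission rates will be compared across groups with contingency tables and differences tested with" chi-square.
- **Second paragraph.** "A linear mixed model approach will be used to assess differences in the primary and secondary outcomes between the two study groups". For binary outcomes: "Logistic regression will be used to assess response and remission rates across the groups".

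Each paragraph states its own rule on one-sided and two-sided testing and its own alpha of 0.05. Neither is called primary, supportive, sensitivity or unadjusted.

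The second paragraph adds: "Medication, education, and intelligence will be taken into account as confounding factors", and says how: "by including them in mixed model and logistic regression model, respectively". Nothing similar is attached to the ANOVA or the chi-square test.

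Elsewhere, Standard Care describes the controls as a subsample of an earlier study, accrued from April 2010 to July 2012, with 30 of 62 to be chosen by matching on sex and age. The Discussion accepts that the non-randomised design could be a source of bias.

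**The concern.** With two tests per outcome and no order between them, the protocol does not say which result answers the hypothesis. The two can disagree for a structural reason: one compares the groups unadjusted and the other adjusts for three factors that the authors regard as confounders. Without randomisation, adjustment can move the estimate as well as its precision.

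The first pair also suits the data less well. Its stated scope is all time points, but the two groups were not seen at the same times. Classical repeated measures ANOVA needs a complete set of visits from each participant, follow-up runs to 24 months, and participants may leave at any time (Ethical Issues). If leaving is related to clinical course, an analysis of completers is biased. A mixed model uses every observed visit and relies on the weaker missing-at-random assumption.

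At stake are a choice of deciding analysis after the results are known, an unadjusted result presented as the main one, and some loss of power.

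**Working it through.** **1. The two paragraphs side by side**

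| | First paragraph | Second paragraph |
|---|---|---|
| Outcomes | primary and secondary | primary and secondary |
| Groups | both study groups | both study groups |
| Continuous | repeated measures ANOVA | linear mixed model |
| Response, remission | chi-square | logistic regression |
| Medication, education, intelligence | not mentioned | included |
| Alpha | 0.05 | 0.05 |
| Stated role | none | none |

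**2. Visit schedules**

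- Robin group (Study Design; Table 1): months 0, 2, 4, 6, 12, 24.
- Controls (Standard Care): months 0, 6, 12, 24, 36.
- Shared: months 0, 6, 12, 24.

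On the six-visit Robin schedule no control has complete data, so a two-group ANOVA is possible only on the four shared visits.

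**3. Error rate if either test may be claimed**

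With one named test the rate per outcome is 0.05. With two, it depends on the correlation between the test statistics, which is assumed here (bivariate normal; one-sided to two-sided values).

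| Assumed correlation | Chance that at least one is significant |
|---|---|
| 0.95 | 0.063 to 0.065 |
| 0.90 | 0.068 to 0.071 |
| 0.70 | 0.080 to 0.084 |
| 0 (upper limit) | 1 − 0.95² = 0.0975 |

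Two tests on the same data should be strongly correlated, so the top rows are the relevant ones.

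**4. Complete cases**

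Input: 30 per group (Sample Size). The article gives no missingness rate, so a rate m per visit is assumed, independent over the three shared follow-ups. Complete cases = 30 × (1 − m)³.

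- m = 5%: 30 × 0.95³ = 25.7
- m = 10%: 30 × 0.90³ = 21.9
- m = 15%: 30 × 0.85³ = 18.4
- m = 20%: 30 × 0.80³ = 15.4

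Independence matters. At 10%, if the same people miss every visit, 30 × 0.90 = 27 remain. If no one misses more than one visit, 30 × (1 − 3 × 0.10) = 21 remain.

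**5. Power**

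Table 2 gives 17 per group for SIPS, 16 for SPI-CY and 27 for SWE; the GAF row is not legible in the copy at hand. The article states neither the SDs nor the power, so these figures cannot be reproduced. Assuming 80% power and a two-sided 5% two-sample t-test, the standardised difference d implied by each N, and the power at other N (noncentral t), are:

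| Instrument | N in Table 2 | Implied d | n = 30 | n = 27 | n = 22 |
|---|---|---|---|---|---|
| SWE | 27 | 0.777 | 84% | 80% | 71% |
| SIPS | 17 | 0.991 | 97% | 95% | 89% |
| SPI-CY | 16 | 1.024 | 97% | 96% | 91% |

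One-sided at 5%, SWE gives 84%, 80% and 72%, so sidedness hardly matters.

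The fair comparison at 10% missing is between 22 complete cases and the 30 × 0.90 = 27 observed at month 6, the visit used in Sample Size. For SWE that is 71% against 80%, a loss of about 9 percentage points from using completers only.

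**The case against.** The best defence is that the paragraphs read naturally as an unadjusted comparison followed by an adjusted one, which is a common pairing. The plan as a whole does adjust, and matching on sex and age comes before both analyses. That stands in part. A reader might infer that the plan leaves confounding unaddressed, and it does not. What is missing is any statement of which result decides, and the unadjusted tests are given the same alpha and the same claim on the outcomes as the adjusted ones. A separate analysis plan could settle the order, but only by demoting a paragraph that the article states as planned inference.

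A reader might also infer that the plan intends to discard incomplete cases. The article does not say so; it states no missing-data rule for either pair. Complete-case use is the default behaviour of classical repeated measures ANOVA, and handling of missing data may be set out elsewhere. Nor does it carry over to the chi-square test in the same way, since that needs only the outcome at one visit. The weakness of the chi-square test is the missing adjustment.

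Third, it is tempting to set 71% against the 84% available with all 30 per group. That overstates the harm of the ANOVA, because any analysis of month 6 loses the participants missing at month 6. SWE is also the most demanding of the legible instruments.

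Finally, deleting every unadjusted result would have a cost, which the fix takes into account.

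**Conclusion.** The point holds on the text. The article fixes two inferential analyses for each outcome at alpha 0.05 without an order. The first omits the confounders that the plan itself names, in a non-randomised historical comparison matched on two factors, and its ANOVA cannot be run over all time points as written.

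The numerical consequences are moderate and rest on assumptions. If either result could be claimed, the error rate per outcome is about 0.063 to 0.071 for test correlations of 0.95 to 0.90. At 10% missing per visit, about 22 of 30 per group are complete (21 to 27 depending on overlap), and SWE power is about 71% rather than 80%, if 80% was planned with 27 per group. SIPS and SPI-CY stay near 89% and 91% on the same basis, so the figures do not show that the trial as a whole is underpowered. The size of any confounding bias cannot be worked out from the article.

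**What to change.** 1. Name the linear mixed model, adjusted for medication, education and intelligence, as the deciding analysis for continuous outcomes. Use all available data at the shared visits (0, 6, 12 and 24 months), with visit as a categorical factor and a group-by-visit term.
2. Name adjusted logistic regression as the deciding analysis for response and remission.
3. Take Cohen's d and its confidence interval from the model contrasts. Keep contrasts at 6, 12 and 24 months, since Hypotheses 2 and 3 are set at all three.
4. Drop repeated measures ANOVA. Keep chi-square, or any other unadjusted comparison, only as a labelled supportive result.
5. Keep the software statement, which now sits in the first paragraph.

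The cost is a text edit, as the replacement methods are already in the plan. There is a small downside. With 30 per group and three covariates, logistic estimates may be unstable if events are few. Medication is recorded at every visit (Table 1), so adjusting for values recorded during treatment may remove part of the effect. For both reasons a labelled unadjusted result should stay.
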